### Statistical analysis

Data will be stored electronically and analyzed using the R software. A 2-sided *P* < 0.05 will be used as the statistical significance threshold. For continuous variables with nonparametric distribution, the data will be expressed as medians and IQRs, and the Mann-Whitney test will be used to compare outcomes. For variables with normal distribution, the data will be expressed as means and SDs, and the *t* test will be used to compare outcomes. The between-group differences will be reported as mean differences with 95% CIs. Two-sided significance tests will be applied to all analyses.

We will compare dichotomous data using the 2-tailed *χ*^2^ test when the number of variables is more than 5 and using the Fisher exact test when the number of variables is equal to or less than 5. We will calculate relative risks and 95% CIs using the 2 × 2 table method with log-linear regression and a normal approximation for the SE.

The survival analysis of the primary outcome will be tested based on the intention-to-treat principle using the Kaplan–Meier method, and the existence of statistical significance between the survival curves will be compared using a log-rank test. Subgroup analyses will be performed to identify potential modifiers of the intervention effect, including gender, age, smoking history, comorbidities, inflammatory indicators, antibiotics use, the feature of chest X-ray or computed tomography (CT) image, the way of oxygen therapy, and the severity scores.

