#### Objectives

Recently, the possibility of using mNGS to identify non-sterile site specimens in the respiratory tract has been discussed, though there are still conflicting opinions. The purpose of this study is to evaluate the effectiveness and consistency of bronchoalveolar lavage fluid (BALF) mNGS in diagnosing and treating pulmonary infections in comparison to conventional testing methods. Furthermore, the aim is to demonstrate whether the combination of mNGS and traditional testing methods could decrease 28-day all-cause mortality with moderate cost-effectiveness.

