### Outcomes

The primary outcome is 28-day all-cause mortality. The secondary outcomes are (1) ICU and hospital length of stay (LOS), (2) ventilator-free days and ICU-free days, (3) consistency between mNGS and traditional microbiological tests, (4) detective rate of mNGS and traditional microbiological tests, (5) turn-out time, (6) types and duration of anti-infective regimens, (7) time from group allocation to start of treatment, (8) duration of vasopressor support, (9) source of drug-resistant bacteria or fungi, and (10) ICU cost.

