### Sample size

In this study, a randomized controlled trial design is used to evaluate the treatment effect of mNGS and traditional microbiological tests in patients with severe pneumonia. According to a previous report [9], we hypothesized the 28-day all-cause mortality of study group and control group to be 15% and 33%, respectively. We assumed that *α* = 0.05 (two-sided test) and *β* = 0.20. Eighty-five patients should be recruited in each group. Considering an attrition rate of 10%, the eligible participants in each group should be 96. Therefore, we determined that the sample size should be 95 in each group (*n* = 192 in total).

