Studies regarding the cost-effectiveness of mNGS assays for pathogen detection are lacking. Relative to most traditional microbiological tests, mNGS testing is expensive. The incremental costs of testing are minimal, compared to the costs of intensive care unit stays or myriad diagnostic tests, not to mention use of even more expensive and advanced anti-infective drugs that are ordered for complex cases. Our study will evaluate the cost-effectiveness data of mNGS testing in severe pneumonia.

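### A skewed ICU cost would be tested by Mann-Whitney, which does not address the mean cost difference that the cost-effectiveness aim needs; the two can part when the arms' cost distributions differ in shape

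*Protocol article*

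**What the plan says.** The Outcomes section closes its list of ten secondary outcomes with "9) source of drug-resistant bacteria or fungi, and (10) ICU cost". Under Objectives, the trial asks whether adding mNGS "could decrease 28-day all-cause mortality with moderate cost-effectiveness", and the Discussion commits to the economic question: "Our study will evaluate the cost-effectiveness data of mNGS testing in severe pneumonia".

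The Statistical analysis section gives one rule for continuous variables, split by distribution. For non-normal variables, "the data will be expressed as medians and IQRs, and the Mann-Whitney test will be used to compare outcomes". For the rest: "For variables with normal distribution, the data will be expressed as means and SDs, and the *t* test will be used to compare outcomes". The next sentence reads "The between-group differences will be reported as mean differences with 95% CIs", without saying whether it covers both kinds of variable or only the normal ones. The threshold is common to all: "A 2-sided *P* < 0.05 will be used as the statistical significance threshold". ICU cost is not singled out anywhere.

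**The concern.** An incremental cost is a difference in arithmetic means, because the mean times the number of patients is what a payer spends. Mann-Whitney asks something else: whether a randomly chosen study patient is as likely to cost more as to cost less than a randomly chosen control patient. For cost data, usually right-skewed, the two questions can have different answers.

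The sentence on mean differences does not settle the matter on either reading.

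- **It covers skewed variables too.** ICU cost then gets a mean difference with a CI and, beside it, a P value for a different quantity. The two can conflict.
- **It covers normal variables only.** This document then plans no mean cost difference for a skewed ICU cost.

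At stake is whether the cost comparison answers the cost question the trial sets itself.

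**Working it through.** **Inputs.** From the protocol: 192 patients allocated 1:1, so 192 / 2 = 96 per arm; two-sided 0.05. The protocol gives no mean, SD or skewness for ICU cost, so there is no cost figure of its own to reproduce. Assumed: log-normal cost, mean scaled to 1 in the control arm, control log-SD σ₀ = 1.0.

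**Step 1: equal means, possibly different shapes.** A log-normal variable with mean 1 has log-mean −σ²/2 and median exp(−σ²/2). The quantity that Mann-Whitney targets is

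θ = P(study > control) = Φ( [(σ₀² − σ₁²)/2] / √(σ₀² + σ₁²) ).

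For σ₁ = 0.7: (1 − 0.49)/2 = 0.255; √1.49 = 1.221; θ = Φ(0.209) = 0.583. The mean costs are identical, yet the rank hypothesis θ = 0.5 is false.

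The approximate standard error of the estimated θ is √[(2n + 1)/(12n²)] = √[193/(12 × 9,216)] = 0.0418. The expected z is (0.583 − 0.5)/0.0418 = 1.98, so the rejection rate is about Φ(1.98 − 1.96) = 51%. The same steps for the other shapes, with simulation beside them:

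| Study log-SD | Median, control v study | θ | Mann-Whitney, formula | Mann-Whitney, simulated | Welch, simulated |
|---|---|---|---|---|---|
| 1.0 | 0.61 v 0.61 | 0.500 | 5% | about 5% | about 5% |
| 0.9 | 0.61 v 0.67 | 0.528 | 10% | 10% | about 5% |
| 0.8 | 0.61 v 0.73 | 0.556 | 27% | 26% | about 5% |
| 0.7 | 0.61 v 0.78 | 0.583 | 51% | 51% | about 6% |

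The first row matters: skewed but identically shaped distributions keep the 5% level.

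**Step 2: a fee for every study patient, offset by savings in the upper tail.** With log-SD 1.0 and mean 1, the 80th percentile is exp(−0.5 + 0.842) = 1.407. The mean excess above it is Φ(1 − 0.842) − 1.407 × 0.20 = 0.563 − 0.281 = 0.281. A 25% saving on that excess is worth 0.25 × 0.281 = 0.07 of mean cost, and a 50% saving 0.14. A fee of the same size leaves the means equal. Simulated at 96 per arm:

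| Fee, share of mean cost (means equal) | Mann-Whitney | Welch |
|---|---|---|
| 1% | 5% | about 5% |
| 2% | 5-6% | about 5% |
| 3% | 7% | about 5% |
| 5% | 10% | about 5% |
| 7% | 15-16% | about 5% |
| 14% | 42-45% | 5-6% |

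With a 10% fee and the 50% tail saving, the study arm's mean is 1 + 0.10 − 0.14 = 0.96, that is 4% lower, yet Mann-Whitney is significant in the direction of study costlier in about 24% of trials. With a 1-3% fee and the same saving, the study mean is 11-13% lower and that happens in only about 3-5%.

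**Step 3: the reverse.** With equal medians and mean costs 15-49% apart (log-SD 0.8 v 0.6, 1.0 v 0.7 and 1.2 v 0.8), Mann-Whitney rejects about 5%, so a real difference in mean cost goes unseen.

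**The case against.** Much of the other side stands.

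- **Skewness is not enough.** A reader might infer that any skewed cost makes the test misleading. It does not: with equal shapes Mann-Whitney holds its level. Different shapes are plausible, since only the study arm has the extra test and its ICU stays may change, but nothing in the document fixes how different they would be.
- **The fee may be small.** A reader might infer that the test's price alone will make mNGS look significantly dearer. The Discussion describes the added cost of testing as very small next to ICU stays. At fees of 1-5% of mean cost the rejection rate is only about 5-10%; rates of 15-45% need fees of 7-14%, which sit badly with that description. Nor does the document say that the mNGS fee is booked under ICU cost, since sequencing is done by an outside laboratory.
- **No cost-effectiveness ratio is described.** A reader might infer that a Mann-Whitney P value or a median will feed such a ratio. The document does not say so, and a separate economic analysis may sit in the full protocol or analysis plan, which is not shown. Its absence here is no fault.
- **A mean difference may already be planned.** On the wider reading of that sentence it is, and a reader of the results could see a conflict with the P value. The planned test would still address another quantity.

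What the objections leave untouched is the rule itself. It is stated, it is the only one that covers ICU cost here, and its test does not match the cost aim.

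**Conclusion.** The point holds in limited form. For a non-normal ICU cost, the stated summary and test do not address the difference in mean cost, and the sentence on mean differences leaves either a P value and CI on different quantities or no mean difference at all.

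The size depends on how far the arms' cost shapes differ: from no inflation with equal shapes to about 51% at log-SD 1.0 against 0.7. In the fee-and-savings model, the lower end (about 5-10%) is closer to what the Discussion implies. All of this rests on assumed log-normal costs, 96 per arm and equal means; it shows what can happen, not what will. A rejection in these settings is right for ranks and becomes an error only when read as a statement about mean cost.

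Severity is low: ICU cost is one of ten secondary outcomes, and the primary mortality analysis and sample size are untouched.

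**What to change.** In Statistical analysis, exempt ICU cost from the choice of test by normality. State that the arms will be compared by the difference in arithmetic mean ICU cost with a bootstrap (or Welch) 95% CI, and that medians and IQRs for cost are descriptive only. In the same edit, say whether the sentence on mean differences applies to non-normal variables in general.

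This costs one or two sentences and a little analysis work, with no extra data or patients. The small downside is that the interval for the mean of a skewed cost may be wide. The change is best made before any comparison of cost by arm is seen.

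### Length of stay and treatment durations end at death, but the plan compares them with plain two-sample tests, so the results are confounded with the mortality difference the trial expects

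*Protocol article*

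**What the plan says.** The Statistical analysis section of the protocol article sorts continuous variables by distribution. For skewed ones, "the data will be expressed as medians and IQRs, and the Mann-Whitney test will be used to compare outcomes". Normally distributed ones are summarised by means and SDs and compared with a t test. The next sentence adds: "The between-group differences will be reported as mean differences with 95% CIs". Kaplan-Meier curves and the log-rank test are named for the primary outcome only, and no rule is given for patients who die before a stay or treatment ends.

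The Outcomes section lists ICU and hospital length of stay, ventilator-free and ICU-free days, and types and duration of anti-infective regimens. It ends with "8) duration of vasopressor support, (9) source of drug-resistant bacteria or fungi, and (10) ICU cost".

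Under Sample size: "we hypothesized the 28-day all-cause mortality of study group and control group to be 15% and 33%, respectively". The Objectives ask whether adding mNGS "could decrease 28-day all-cause mortality with moderate cost-effectiveness", and the Discussion says "Our study will evaluate the cost-effectiveness data of mNGS testing in severe pneumonia".

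**The concern.** A stay, a vasopressor course and an antibiotic course all end when the patient dies. A Mann-Whitney or t test on the raw durations treats a death on day 4 exactly like a discharge on day 4. When mortality is equal in the two arms this does little harm. Here the trial is built on an 18-point difference, so the arms would contain very different proportions of stays cut short by death.

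A difference in length of stay could then mean quicker recovery, slower recovery or simply a different number of deaths, and the planned test cannot tell which. If deaths come early, a test that saves lives and changes nothing else could be reported as prolonging stay and treatment. ICU cost raises a separate question. A death does not make the recorded cost wrong, but a rank test on skewed cost does not address mean incremental cost, which is what a cost-effectiveness aim needs.

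**Working it through.** **1. The plan's own figure.** Inputs from Sample size: p1 = 0.15, p2 = 0.33; "We assumed that *α* = 0.05 (two-sided test) and *β* = 0.20". Two proportions, unpooled normal approximation:

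n = (1.960 + 0.842)² × [0.15 × 0.85 + 0.33 × 0.67] / 0.18² = 7.849 × 0.3486 / 0.0324 = 84.4, so 85 per group. This matches the article. These outcomes did not drive the sample size.

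**2. Expected deaths.** At 85 per group: 0.15 × 85 = 12.8 and 0.33 × 85 = 28.1. At 96 per group (192 in total): 14.4 and 31.7. The control arm would have roughly twice as many stays ended by death.

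**3. Shift caused by mortality alone.** Suppose stays of survivors are the same in both arms, and likewise stays of decedents. Then

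mean(study) − mean(control) = (0.33 − 0.15) × (survivor mean − decedent mean) = 0.18 × gap.

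| Gap, survivor minus decedent mean (days) | Shift in mean stay with mNGS (days) |
|---|---|
| 10 | +1.8 |
| 5 | +0.9 |
| 0 | 0 |
| −4 | −0.7 |

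The sign follows the sign of the gap, which the documents do not give.

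**4. How often the planned test would react.** Everything about stays here is an assumption: log-normal, sigma 0.7, survivor median 12 days in both arms, 96 per arm, mortality 15% versus 33%, two-sided Mann-Whitney at 0.05.

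| Decedent median (days) | mNGS significantly longer | mNGS significantly shorter |
|---|---|---|
| 4 | about 35% | almost never |
| 6 | about 18% | almost never |
| 9 | about 6% | under 1% |
| 12 | about 2.5% | about 2.5% |
| 15 | about 1% | about 6% |

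Repeat runs agree to within about two percentage points. With a decedent median of 6 days the average arm medians are 11.0 versus 9.7 days, although mNGS has no effect on any survivor's stay. As a check on the mean, the log-normal mean is the median × exp(0.7²/2) = median × 1.278, so the shift is 0.18 × (12 − 6) × 1.278 = 1.4 days.

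**5. Sensitivity.** A second set of assumptions (85 per arm, survivor sigma 0.6, decedent sigma 0.7 with stays capped at 28 days) gives significantly longer stay in 31%, 16% and 8% of trials for survivor/decedent medians of 14/5, 14/8 and 14/10 days, and 33% for 20/7. There is no bias in the test at 14/14. At 10/14 the result reverses, with 8% significantly shorter. If mNGS also cuts survivors' stay by 20% (control medians 14/7), the study arm is significantly shorter in 11% and longer in 0.5%, so a real benefit can offset the bias.

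**6. A measure that penalises death.** With ICU-free days to day 28 and death scored 0 (my rule; the article states none), the study arm is significantly better in 34% to 50% of trials in all six scenarios with equal survivor stays, and significantly worse in almost none. The direction no longer depends on when deaths occur.

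**The case against.** **Direction.** A reader might infer that the plan will make mNGS look worse. The documents do not support that: they contain no stay or duration data, and steps 3 to 5 show the bias shrinking, vanishing or reversing. Only the conditional statement stands.

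**Handling of deaths.** The article assigns tests by distribution, not outcome by outcome, and a Mann-Whitney test could be run with deaths ranked worst. Such detail may sit in an analysis plan that is not shown. But a t test or Mann-Whitney on a duration, taken as written, uses the duration as observed, and time-to-event methods are expressly tied to the primary outcome.

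**Existing cover.** Ventilator-free and ICU-free days are listed and usually penalise death. They partly cover ventilation and ICU stay. They do not cover hospital stay, vasopressor duration or anti-infective duration.

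**Not a false-positive rate.** In these scenarios the distributions of stay really differ, and the test detects that. Plain length of stay is also a legitimate measure of resource use. Both points are right; the difficulty is reading the result as recovery.

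**Cost.** A reader might infer that death biases the cost comparison and that the cost-effectiveness aim cannot be answered. Neither follows. A decedent's ICU cost is a real cost and belongs in the comparison. The mean-difference sentence may already promise mean incremental cost, mortality by arm will be known, and a joint economic plan may exist elsewhere.

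**P-value and interval.** One could read a rank p-value as paired with a mean-difference interval for skewed outcomes. The sentence follows directly on the t-test sentence and may apply only there, so this is an ambiguity and not a demonstrated error.

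**Conclusion.** The point holds for ICU and hospital length of stay, vasopressor duration and anti-infective duration: under the trial's own hypothesis of 15% versus 33% mortality, the named tests confound these outcomes with the primary outcome. Mortality alone moves mean stay by 0.18 times the survivor-minus-decedent gap. Under the assumed stays in step 4, significantly longer stay with mNGS appears in about 6% to 35% of trials when deaths come earlier than survivors' discharge; there is no bias when the two are equal and a reversed sign when decedents stay longer. These sizes rest wholly on assumed stay distributions; the confounding itself does not.

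For ICU cost the point is narrower: a rank test is the wrong basis for a cost-effectiveness aim, while counting decedents' costs is correct. This is a worthwhile improvement to secondary analyses. The primary analysis and the sample size are unaffected.

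**What to change.** - **ICU and hospital stay:** analyse as time to discharge alive with death as a competing event, for example cumulative incidence curves with a Gray test or Fine-Gray model. Keep plain length of stay as a descriptive summary of resource use.
- **Vasopressor and anti-infective durations:** analyse as days alive and free to day 28, with death scored as the worst value. State the same death score for ventilator-free and ICU-free days. These measures combine mortality with duration by design, so show deaths and survivors' durations descriptively beside them.
- **ICU cost:** base the comparison on the difference in arithmetic mean cost per randomised patient, including the mNGS test, with a bootstrap confidence interval. Report it jointly with the 28-day mortality difference.
- **Wording:** say which outcomes the mean-difference sentence covers.

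The cost is revised analysis wording and modest extra programming. The data needed are stay and treatment dates, vital status, ICU cost and the unit price of mNGS. The downside is that some summaries will be less familiar to clinicians. The choice should be fixed before outcomes by arm are seen, because a later switch would look data-driven.

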## Method

### Study design

This study is a regional, multi-center, open, prospective, randomized controlled trial that will include patients with severe pneumonia, from four large tertiary hospitals in North China. A total of 192 participants will be enrolled and randomly assigned in a 1:1 ratio to either the study group (mNGS combined with traditional microbiological tests group) or the control group (traditional microbiological tests group) using the central randomization system. Patients will be provided anti-infective treatment based on clinical experience according to mNGS + traditional tests or traditional tests only for two groups. The NT-BALF trial will be conducted according to the principles of the Declaration of Helsinki [7]. The Institutional Review Board of Peking Union Medical College Hospital, Chinese Academy of Medical Sciences & Peking Union Medical College in Beijing, China, approved the trial protocol (version 4.0, reference number I-23PJ1316, date 15 August 2023). The flowchart of the protocol is shown in Fig. 1. The schedule of enrolment, intervention, and assessments following the Standard Protocol Items: Recommendation for Interventional Trials (SPIRIT) guidelines (Additional file 1) is presented in Fig. 2.

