### Intervention

For both groups, bronchoalveolar lavage fluid will be harvested within 24 h of participants entering the ICU. Traditional microbiological tests will be collected as soon as possible after admission and will be performed in local in-house laboratories. Traditional microbiological tests, including culture, antigen detection, multiplex PCR, and direct microscopic examination of specimens. The results of traditional microbiological tests will be interpreted according to standard procedures.

BALF specimens will be divided into aliquots and used for both mNGS tests and traditional microbiological tests for study group. BALF mNGS tests will be transferred to the same professional genomic laboratory independently by cold chain transportation. The genomic laboratory will perform nucleic acid extraction, library construction, amplification and sequencing, bioinformatic analysis, and data interpretation according to previous clinical practice.

In the study group, anti-infective treatment regimen is based on both BALF mNGS and traditional microbiological tests, while in the control group, it is based on the results of traditional microbiological tests. The results of mNGS and necessary clinical data will be judged by a group of senior clinicians, who reached a unified opinion.

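### The stated chi-square/Fisher rule for dichotomous data does not fit the within-patient comparison of mNGS and traditional detection rates in the study group

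*Protocol article*

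**What the plan says.** All references are to the protocol article.

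- **Objectives.** Part of the purpose is to "evaluate the effectiveness and consistency of bronchoalveolar lavage fluid (BALF) mNGS in diagnosing and treating pulmonary infections in comparison to conventional testing methods".
- **Outcomes.** Secondary outcome 3 is "consistency between mNGS and traditional microbiological tests". Secondary outcome 4 is "detective rate of mNGS and traditional microbiological tests".
- **Intervention.** "BALF specimens will be divided into aliquots and used for both mNGS tests and traditional microbiological tests for study group". Control patients also have lavage and traditional tests, but no mNGS.
- **Statistical analysis.** The rule for binary outcomes begins "We will compare dichotomous data using the 2-tailed" and names the chi-square test, with Fisher's exact test for small numbers. Relative risks with 95% CIs come from a 2 × 2 table. The rule makes no exception for paired results, and the section names no paired method.

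**The concern.** Chi-square, Fisher and the usual 2 × 2 relative risk treat the two proportions as coming from different people. In the study group each patient supplies both an mNGS result and a traditional result from one specimen. An unpaired analysis would count 96 patients as 192 independent observations and ignore the covariance between the two results.

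Two methods applied to one specimen should tend to agree, so the covariance should be positive. The unpaired standard error is then too large, the interval too wide and the test too cautious. At stake is the precision of the test-against-test comparison, which belongs to the stated purpose. Consistency is a further point: a chi-square test examines difference or association and does not measure agreement.

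**Working it through.** **1. The plan's own figure.** The article gives no detection rate, correlation or power for outcomes 3 and 4. Its only calculation is for mortality (33% vs 15%, two-sided alpha 0.05, power 80%). With unpooled variance:

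(1.96 + 0.8416)² × (0.33×0.67 + 0.15×0.85) / 0.18² = 7.849 × 0.3486 / 0.0324 = 84.4, so 85 per group, as stated.

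Dividing by 0.90 for attrition gives 94.4, so 95; the article states 96 for eligible participants per group. This matters here only because it sets the number of pairs at about 96.

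**2. Inputs.** From the article: about 96 study-group patients, two-sided alpha 0.05. Assumed, because the article is silent: the detection rates and how the pairs split. Let *a* be the proportion positive on both tests, *b* on mNGS only and *c* on traditional only. Then p₁ = a + b and p₂ = a + c.

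**3. Standard errors for one assumed case** (a = 0.53, b = 0.22, c = 0.07, so 75% vs 60%):

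- Unpaired: √[(0.75×0.25 + 0.60×0.40)/96] = √(0.4275/96) = 0.0667, a 95% half-width of 13.1 points.
- Paired: √{[b + c − (b − c)²]/96} = √(0.2675/96) = 0.0528, a half-width of 10.3 points.

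**4. Power for 75% vs 60%**, by simulating 96 pairs. The correlation is phi = (a − p₁p₂)/√[p₁(1−p₁)p₂(1−p₂)] = (a − 0.45)/0.2121.

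| b, c, a | phi | Unpaired chi-square | McNemar (asymptotic) |
|---|---|---|---|
| 0.25, 0.10, 0.50 | 0.24 | 62% | 72% |
| 0.22, 0.07, 0.53 | 0.38 | 63–64% | 82% |
| 0.20, 0.05, 0.55 | 0.47 | 64–65% | 88% |

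Ranges reflect simulation error between runs.

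**5. Rejection rate with no true difference** (both rates 65%). With equal margins the unpaired statistic has variance 1 − phi, so its true size is about 2[1 − Φ(1.96/√(1 − phi))], where phi = (a − 0.4225)/0.2275.

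| b, c, a | phi | Formula | Simulated |
|---|---|---|---|
| 0.10, 0.10, 0.55 | 0.56 | 0.3% | 0.3–0.4% |
| 0.15, 0.15, 0.50 | 0.34 | 1.6% | 1.6–1.7% |
| 0.20, 0.20, 0.45 | 0.12 | 3.7% | 3.6–3.7% |

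Asymptotic McNemar stays close to 5% in all three.

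**6. Sensitivity.**

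- Large difference (b = 0.30, c = 0.05, a = 0.50; 80% vs 55%): 98.6% unpaired against 99.6% McNemar. The loss nearly vanishes.
- Other margins (65% vs 50%): 57% against 71% at phi 0.3, and 58% against 86% at phi 0.5.
- The exact McNemar test recovers less: 64% and 80% in those last two cases.
- Negative correlation reverses the direction: with both rates at 50% and phi −0.2, the unpaired test rejects 7.5% of the time.

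**7. Agreement.** With both detection rates at 50%, chance agreement is 0.5, so kappa = (observed agreement − 0.5)/0.5. Observed agreement can be anything from 0 to 1, so kappa can run from −1 to +1 while the two rates are identical. Comparing the rates therefore says nothing about consistency.

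**The case against.** The strongest reply is that the Statistical analysis section never links its binary rule to mNGS, detection or consistency. The surrounding text speaks of between-group differences, and for study against control the rule is valid. The article may also leave methods for individual secondary outcomes to an analysis plan that is not shown. This stands in part. The missing agreement statistic would not be a finding on its own, and a reader who infers that consistency will be tested by chi-square, or will get no valid estimate, goes beyond the text. What remains is that the article states a rule for dichotomous data without qualification, and the rule does not fit one natural reading of a named outcome.

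Three other stronger readings are also unsupported:

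- **The control group cannot contribute.** Control patients do have traditional-test results. Outcome 4 does not say whether its comparison is within patients or between arms, and a between-arm comparison of diagnostic yield is independent and suits chi-square/Fisher. Control patients cannot contribute pairs, which is a narrower statement.
- **The trial risks a false claim for mNGS.** With the positive correlation expected from one specimen, the error runs the other way. Inflation needs negative correlation, and nothing in the article suggests it.
- **The main result is threatened.** The mortality outcome has its own intention-to-treat Kaplan–Meier and log-rank analysis, and the sample size rests on mortality alone.

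**Conclusion.** The point holds as a conditional one, at moderate severity. If the stated rule is applied to the mNGS-versus-traditional detection comparison within the study group, it ignores the pairing. With positive correlation the result is conservative. For an assumed 15-point difference (75% vs 60%) the cost is about 10 to 24 points of power (72 − 62 to 88 − 64).

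The size rests on assumed detection rates, an assumed positive correlation and 96 complete pairs. Weak correlation or a large true difference makes the loss small. Outcomes 3 and 4 are two of ten secondary outcomes, and no conclusion on mortality depends on them.

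**What to change.** In the Statistical analysis section, or in the analysis plan before any analysis is run:

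- State that the within-study-group comparison of mNGS and traditional detection rates uses McNemar's test (exact if discordant pairs are few), with the paired difference and its 95% CI.
- State that consistency is reported in the same pairs as Cohen's kappa with positive and negative percent agreement, each with a 95% CI.
- Keep chi-square/Fisher and 2 × 2 relative risks for between-arm comparisons. If outcome 4 is also meant as diagnostic yield by randomised arm, say so and list it separately.
- Do not mix control-group traditional results into the paired comparison.

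The cost is wording only. The design already produces the paired results, so no extra patients, samples or tests are needed.

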### Randomization and blinding

Stratified block randomization will be performed centrally in a 1:1 ratio using the SAS software (SAS Institute, Inc., Cary, NC, USA). Within each stratum, a random block size of 4 will be used. Considering the nature of antibiotic intervention, this study is open to the clinicians, patients, and investigator; only the data analyst and follow-up evaluator will be blinded.

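### The 28-day mortality analysis names no adjustment for randomisation strata or baseline severity: valid, but it may give up some precision

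*Protocol article*

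**What the plan says.** Under Randomization and blinding, the article states: "Stratified block randomization will be performed centrally in a 1:1 ratio". Blocks of 4 are used within each stratum, but the stratification factors are not named.

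Under Outcomes: "The primary outcome is 28-day all-cause mortality". Under Sample size: "we hypothesized the 28-day all-cause mortality of study group and control group to be 15% and 33%, respectively". The size is therefore set on a comparison of two proportions.

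Under Statistical analysis, the primary outcome is assessed by intention to treat with Kaplan-Meier curves, and "the existence of statistical significance between the survival curves will be compared using a log-rank test". Dichotomous data in general are compared by chi-square or Fisher test, with relative risks obtained "using the 2 × 2 table method with log-linear regression and a normal approximation for the SE". None of these sentences mentions a stratum or a covariate. Baseline prognostic variables enter only as subgroup factors; that list includes age and comorbidities and ends with "the way of oxygen therapy, and the severity scores".

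**The concern.** When randomisation is stratified, the usual analysis carries the strata, and it is good practice to adjust for one or two strong baseline predictors of the outcome. Here eligibility runs from patients who meet three minor criteria to patients with septic shock or on mechanical ventilation, so baseline risk of death is likely to vary widely. Severity scores are planned for, but only to split the sample.

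At stake is precision. About 46 deaths are expected (96 × 0.15 + 96 × 0.33 = 46.1), and after the 10% attrition allowance the crude comparison has only about the planned power. If severity is strongly prognostic, the same patients could give a narrower interval and a better chance of detecting the effect.

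**Working it through.** **Inputs from the article.** Mortality 15% and 33%; "We assumed that *α* = 0.05 (two-sided test) and *β* = 0.20"; 85 per group before attrition and 96 after (192 in total); four hospitals; blocks of 4.

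**Assumed, because the article is silent.** Prognostic strength of severity: AUC 0.60 to 0.80 for 28-day death. Strata: four, standing in for the hospitals, with a between-centre SD of 0 to 0.6 on the log-hazard scale.

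**1. The plan's own figure.** With the unpooled two-proportion formula,

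n = (1.96 + 0.8416)² × (0.15 × 0.85 + 0.33 × 0.67) / 0.18² = 7.849 × 0.3486 / 0.0324 = 84.4, so 85.

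This matches "Eighty-five patients should be recruited in each group". The trial was sized on a crude comparison.

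**2. Power of the crude analyses.**
- Chi-square: Φ{[0.18√n − 1.96√(2 × 0.24 × 0.76)] / √0.3486}. For n = 85 this is Φ(0.806) = 79.0%; for n = 96 it is Φ(0.982) = 83.7%.
- Log-rank (Schoenfeld): HR = ln 0.85 / ln 0.67 = 0.406, and power = Φ(½√D × |ln HR| − 1.96). With D = 170 × 0.24 = 40.8 deaths this is 82.1%; with D = 192 × 0.24 = 46.1 it is 86.5%.

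The crude plan therefore delivers about what it promises.

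**3. Adjusting for severity, Cox model.** 2,500 simulated trials per row, marginal risks held at 33% and 15%:

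| Assumed severity AUC | N = 192: log-rank → adjusted | N = 170: log-rank → adjusted |
|---|---|---|
| 0.60 | 83.5% → 83.0% | 81.0% → 80.9% |
| 0.66 | 82.4% → 85.2% | 80.2% → 81.1% |
| 0.74 | 84.0% → 90.0% | 80.4% → 85.2% |
| 0.80 | 84.8% → 94.0% | 79.4% → 90.0% |

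The simulation error of one power figure is about √(0.84 × 0.16 / 2500) = 0.7 points, so the first row shows no difference. The Cox hazard ratio is conditional on severity, so this table shows a gain in power and not a narrower interval for a marginal effect.

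**4. The analysis proposed below.** Logistic standardisation with strata, severity and age at N = 192 moved power from 84.0% to 84.2% with weak severity prognosis, and from 85.7% to 91.1% with strong prognosis. The standard error fell by about 1% to 8%. As a cross-check, an 8% smaller standard error is a variance reduction of 1 − 0.92² = 15%. In the chi-square formula, n = 96 / 0.85 = 112.9 gives 89.2% against 83.7%, a gain of similar size.

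**5. Strata alone.** Stratifying the log-rank test by four centres added nothing when centres did not differ, 0.7 to 0.8 points at SD 0.3, and 1.6 to 2.4 points at SD 0.6.

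**6. Type I error.** Under the null, the crude log-rank test rejected in 4.0% to 5.4% of trials, being slightly conservative when strata were strongly prognostic. The stratified log-rank test rejected in 5.0% to 5.9%, and the standardised logistic analysis stayed near 5%.

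**The case against.** The strongest reply is that nothing here is wrong. The article never calls the tests unadjusted; it is a condensed account, and an unseen SAP could add strata and covariates. The sample size rests on a crude comparison, and the crude comparison meets it. The gain depends wholly on assumed prognostic strength, and at AUC 0.60 it vanishes. The strata are unnamed, so a centre effect is a guess. Severity scores appear only in the subgroup list, without instrument or timing, so it is not established that a usable baseline score is collected. Six model terms (treatment, three strata, severity, age) leave about 46 / 6 = 7.7 deaths per term.

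Most of this stands and limits the size of the point. Two parts do not remove it. The article does commit to particular tests for the primary outcome, so the point questions a stated choice; if the SAP adjusts, the two documents need aligning. And the model with strata, severity and age kept its error rate near 5% in simulation, so the number of deaths per term is not an obstacle with four strata.

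A reader might infer three stronger things that the article does not support:
- **That the primary result would be biased or its error rate inflated.** Chance imbalance in severity is already covered by the error rate of a test under randomisation, as step 6 shows.
- **That the trial is underpowered because it does not adjust.** Step 2 shows otherwise.
- **That two rival primary tests leave the decision open.** Only the Kaplan-Meier and log-rank sentence is tied to the primary outcome and to intention to treat; the 2 × 2 paragraph covers dichotomous data generally. Some ambiguity remains, since 28-day mortality is dichotomous and the sample size uses proportions, but it is minor. In simulation at 96 per group, log-rank and chi-square disagreed on significance in 1.4% of trials, and log-rank and Fisher in 4.2%.

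**Conclusion.** The point holds as an efficiency loss. The planned crude analyses are valid and have about the intended power. Adjustment would add about 0 to 6 points of power at N = 192 in the standardised logistic simulations, and up to about 9 points in the Cox simulation at a severity AUC of 0.80. Nearly all of it comes from severity; the strata by themselves add about 0 to 2.5 points.

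These figures rest on the article's 15% and 33%, on an assumed range of prognostic strength, and on four assumed strata. They also require a severity score taken before randomisation. The worst case is essentially no gain, so the change is worth making but the trial does not depend on it.

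**What to change.** Before database lock, and preferably well before it, prespecify one primary analysis: 28-day mortality in all randomised patients, reported as a standardised risk difference and risk ratio from a logistic model with treatment, the randomisation strata, age and one severity score. Name the stratification factors. Name the severity instrument and require that it be scored before randomisation. Report as supportive the Kaplan-Meier curves with a log-rank test stratified by the randomisation strata, and the crude 2 × 2 result.

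The cost is a revision of the analysis text and a little more analysis work, with no additional patients. The one practical condition is that the chosen score is recorded at baseline, which should be checked against the case report form.
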